### Design of Functional Assessment and Self-Report Surveys Testing

The study includes three main forms of data collection: (1) telehealth-delivered performance-based physical function assessments, (2) self-report survey measures, and (3) wearable activity monitoring of daily step counts. Measures were selected following a review of available assessments with an emphasis on usability, accessibility, and relevance for adults with ASD, including consideration of the sensory, cognitive, and motor features that may influence remote assessment participation and performance. A summary of health outcome measures and related International Classification of Functioning, Disability and Health domains is provided in Table 1, and the sequence of outcome measure assessments is provided in Figure 2.

**Table 1 table1:** Outcome measures.

Outcome instrument			Outcomes assessed		ICF^a^-Meade conceptual model domain
Remote performance assessments					
	5xSTS^b^ [29,30]	Lower extremity strength and functional mobility		Body functions and structures	
	30sSTS^c^ [31,32]	Lower body strength and endurance validated for use in remote assessments		Body functions and structures	
	Standing balance (eyes open/closed) [33,34]	Static balance under eyes open and closed conditions; derived from BBS^d^ items commonly used in neurological populations		Body functions and structures	
	SLS-R/L^e^ eyes open, and eyes closed [35]	Balance and vestibular function assessed separately for right and left limbs		Body functions and structures	
	Physical activity (steps/day) Fitbit Inspire 3 (Google LLC) [36-38]	Objective measurement of daily physical activity via step count		Activities	
Self-report survey assessments					
	STEADI^f^-Falls Risk Screening [39]	Multidimensional fall risk screening (mobility, physical function, medical history, environmental hazards, and cognition/mental health)		Health status	
	LEFS^g^ [40,41]	20-item self-report measure of functional status in individuals with lower limb musculoskeletal conditions		Activities/participation	
	PROMIS^h^-PF^i^ [42,43]	Self-reported ability to perform physical activities (short form)		Activities/participation	
	PROMIS-Global Health (general mobility and QoL^j^) [44]	General health status, including physical function, pain, fatigue, emotional distress, and social well-being		Activities/participation; personal factors; QoL	
	PROMIS-IS^k^ [45]	Perceived availability of social and IS		Environmental factors	
	Co-Morbidity Index [46]	Impact of chronic health conditions on functional outcomes		Personal factors	
	GSLT-PAQ^l^ [47]	Self-reported leisure-time physical activity participation		Activities/participation	
	Demographics: age, race, ethnicity, sex, city, state, ZIP code	Age, race, ethnicity, gender, and geographic characteristics (city, state, and ZIP code)		Personal/environmental factors	
SPARK^m^ registration data					
	Social Responsiveness Scale-Autism Severity [48]	Quantitative measure of social impairment associated with ASD^n^ relatively stable trait over time		Body functions activities and participation	

^a^ICF: International Classification of Functioning, Disability, and Health.

^b^5xSTS: Five Times Sit-to-Stand.

^c^30sSTS: 30-Second Sit-to-Stand.

^d^BBS: Berg Balance Scale.

^e^SLS-R/L: right/left single-leg stance.

^f^STEADI: Stopping Elderly Accidents, Deaths, and Injuries.

^g^LEFS: Lower Extremity Functional Scale

^h^PROMIS: Patient-Reported Outcomes Measurement Information System.

^i^PF: physical function.

^j^QoL: quality of life.

^k^IS: instrumental support.

^l^GSLT-PAQ: Godin-Shephard Leisure-Time Physical Activity Questionnaire.

^m^SPARK: Simons Powering Autism Research and Knowledge.

^n^ASD: autism spectrum disorder.

**Figure 2 figure2:**
[figure not shown]
Sequence of outcome measurement. ASD: autism spectrum disorder; ICF: International Classification of Functioning, Disability, and Health; PROMIS: Patient-Reported Outcomes Measurement Information System; SPARK: Simons Powering Autism Research and Knowledge.

Study activities are organized into 2 linked phases within a nested design. Phase 1 focuses on the remote telehealth-based performance assessment component and is completed by a randomized subset of 25 participants drawn from the overall study cohort. Phase 2 includes the full study sample and comprises self-report survey measures and wearable activity monitoring. Thus, all enrolled participants complete the Phase 2 components, whereas the Phase 1 subset additionally completes the remote performance-based assessment protocol.

All participants will complete online survey measures using REDCap and will be mailed a Fitbit Inspire 3 (Google LLC) device to wear for 2 weeks. Daily step-count data will be downloaded through the Fitabase (Small Steps Labs, LLC) platform. Completion of self-report surveys and wearable-monitor compliance for 2 weeks is required for participation in the full study sample. For the nested Phase 1 subset, participation also includes one 60-minute telehealth-based physical function assessment session.

### Phase 1: Validation of Remote Functional Assessments

In Phase 1, a randomized selection of 25 participants will undergo remote telehealth-based physical function assessments via secure platforms using their personal computing devices. The telehealth assessment includes a complete battery of physical function, including the Five Times Sit-to-Stand (5xSTS), 30-second Sit-to-Stand (30sSTS), standing balance (eyes open [EO] and eyes closed [EC]), and Single-Leg Stance (SLS; EO and EC). All assessments will be recorded to support intra- and interrater reliability analyses across 6 independent raters. Feasibility will be evaluated based on completion rates, participant feedback, and technical challenges.

### Rater Training

To assess interrater reliability of video-recorded remote assessments, the primary rater, a licensed physical therapist (PT) with expertise in functional outcome measures and experience working with individuals with ASD, will train 4 second-year and 3 third-year Doctor of Physical Therapy (DPT) students from the same academic institution. Training will include structured instruction on scoring procedures, video-based calibration sessions, and a formal agreement check-off to ensure consistency prior to data collection. All raters will also receive specialized training in safety monitoring tailored to the ASD population.

Calibration will be conducted using 3 mock video-recorded assessments representing the study performance battery. To qualify for independent scoring, each student rater must achieve at least 80% agreement with the primary rater across scored items during the formal check-off. Raters who do not meet this criterion will receive additional feedback and retraining and will repeat calibration until the required agreement level is achieved before scoring study recordings independently.

Although licensed PTs typically administer remote functional assessments, supervised DPT students may contribute as part of their clinical training. Their involvement in this study highlights the potential for integrating student participation into telehealth-based evaluations and may support broader implementation in educational and clinical settings.

### Preremote Session Instructions

Prior to the scheduled session, participants will receive an email with detailed instructions to prepare their environment and equipment. Participants will also be encouraged to log into Zoom (Zoom Video Communications, Inc) a few minutes early to troubleshoot any technical issues. Additionally, given the unique sensory, cognitive, and motor coordination profiles of adults with ASD, additional safety measures will be implemented, and the email will include the following guidance and recommendations when possible:

Chair requirements: a sturdy chair with a seat height of approximately 43-45 cm (knee height), equipped with armrests and a backrest.Open space: a clear, unobstructed area free of tripping hazards to safely perform the tests.Quiet environment: a distraction-free setting to support concentration and communication.Camera setup: the device camera should be positioned to capture the participants’ full body during both seated and standing movements.

### Day of Remote Session Safety Check

Given the unique sensory, cognitive, and motor coordination profiles of adults with ASD, additional safety measures will be implemented. Once the participant and rater have successfully logged into the secure Zoom video platform, the rater will greet the participant; confirm readiness; and identify any sensory sensitivities, communication preferences, or physical limitations that may affect test performance. All raters will ensure the following safety measures and instructions are provided to the study participant to optimize remote testing sessions: (1) new or recent medical conditions, injuries or changes in physical status that may affect test performance; (2) quiet environment, when possible, the study participant will be encouraged to choose a space that is quiet and free from distractions to help with focus during the evaluation; and (3) computer setup, participants will be encouraged to position a computer or device so that the rater can see their entire body during the tests. The camera should also be at a height that allows the rater to see them sitting and standing. If necessary, the rater will use their own device to demonstrate body positioning and spacing expected of the participant. Testing sessions will be paused or discontinued if participants exhibit safety concerns, including but not limited to dizziness, chest pain, shortness of breath, loss of balance, or expressed discomfort. The trained assessor conducting the session will make the determination to pause or terminate testing based on these criteria.

### Remote Video Assessment

Each participant will complete a remote telehealth-based performance assessment session, which will be video-recorded. Following the safety check, the rater may begin the remote-based performance assessment. The evaluation will include standardized performance-based functional assessments, including the 5xSTS test, 30sSTS, modified Berg Balance Scale (BBS) items (standing EC/EO), and SLS test. These assessments will be conducted in real time by a trained rater and are designed to measure lower extremity strength, balance, and functional mobility. The rater will provide the following to optimize testing procedures. First, clear instructions and demonstrations to all study participants will be given. All test procedures will be explained using simple, direct language. Visual demonstrations will be provided, and participants will be allowed to practice each movement before formal testing begins. Second, real-time monitoring will be used, ensuring that the rater continuously monitors participant posture, movement quality, and signs of distress or fatigue. Testing will be paused or discontinued if safety concerns arise. Third, rest breaks will be given. The participants will be offered rest breaks between assessments and trial sets to prevent fatigue and accommodate sensory regulation needs. Video recordings will be used exclusively for evaluation of interrater and intrarater reliability of rater scoring; no repeat participant assessments will be conducted. Interrater reliability will be evaluated by having 6 independent raters score the same recordings. Intrarater reliability will be evaluated by having each rater re-score the same recordings after a 2-5-day interval.

### Performance-Based Outcome Measures

#### 5xSTS

This test assesses lower extremity strength and functional mobility. It has demonstrated appropriate feasibility, strong reliability, and validity in both in-person and remote formats across various populations, including older adults, individuals with chronic conditions, and individuals with cancer [29,30]. Participants will be instructed to sit with their arms folded across their chest and back against the chair. They will be asked to stand up and sit down 5 times as quickly as possible. The time to complete the 5 repetitions will be recorded using a stopwatch. A shorter completion time indicates better lower limb strength [30].

#### 30sSTS

A measure of lower body strength and endurance, the 30sSTS has been validated for use in remote assessments and is sensitive to functional limitations in diverse populations [31,32]. Participants will be instructed to complete as many full stands as possible within 30 seconds. The chair will be placed against a wall to prevent movement. Participants will sit in the middle of the chair with feet shoulder-width apart and arms crossed at the chest. A demonstration will be provided, and participants will practice 1-2 repetitions before the test. If arm use is required, the score will be recorded as zero. The total number of correctly executed stands will be counted silently by the assessor. Partial or incorrect stands will not be included in the final score.

#### Standing Balance Tests (Bipedal Stance, EO/EC)

Participants will perform bipedal stance with EO and EC to assess static balance. This assessment is often associated with one of the 14 testing items from the BBS, a widely used tool to assess balance, especially in patients with neurological diseases [34]. The BBS contains and commonly estimates the risk of falls. It is important to determine the suitability of the BBS, which is frequently used in clinical practice, for telehealth assessment.

Participants will be asked to stand barefoot (if tolerated), with their feet side-by-side and arms crossed over their chest. For EO trials, participants will focus on a visual target at eye level. Timing will begin when the tester says “Go.” For EC trials, participants will close their eyes upon instruction after they are positioned. Each trial will end if the participant moves the feet, uncrosses/moves the arms, opens the eyes during EC, loses balance/uses external support, or reaches the 45-second maximum. Participants will complete 2 trials with EO and 2 trials with EC, alternating conditions to reduce fatigue and habituation. These tests are commonly used in clinical settings and have demonstrated feasibility for remote administration [33].

#### SLS-Right/Left, EO/EC

The timed unipedal stance test (EO/EC) evaluates balance and vestibular function. It has excellent interrater reliability and established normative values [35]. Unipedal balance (30-second SLS) was found to be reliable and valid for in-person functional outcomes assessment of lower extremity strength and balance and has recently been examined for remote assessments [35]. Participants will be asked to stand barefoot (if tolerated) on one limb, with the opposite foot raised near but not touching the stance limb. The arms will be crossed over the chest, and the participants will focus on a visual target at eye level. Timing will begin when the foot is lifted and will end upon any of the following: arm movement away from the chest, foot contact, stance-foot repositioning, loss of balance/use of external support, opening the eyes during EC, or reaching the 45-second maximum. SLS will be performed on both the right and left legs under both EO and EC conditions. Each participant will complete 2 trials per leg per condition (EO: 2 trials right and 2 trials left; EC: 2 trials right and 2 trials left), alternating EO and EC conditions. The order of testing (starting leg and/or condition) will be randomized, and 1-2 minutes of rest will be provided between trial sets. The best time for each leg and condition will be recorded; for analyses, the primary outcome for EO and EC will be the best (longest) time across both legs and all trials (capped at 45 seconds). Average times across trials may also be summarized descriptively.

#### Free-Living Daily PA (Steps/Day)

Steps per day will be assessed using a Fitbit Inspire 3 wearable device, a commercially available wearable activity tracker that records the total amount of steps/day [37]. PA tracking with consumer-based wearables has a relatively high correlation with research-grade accelerometers [49]. At least 7 days of walking activity data (5 weekdays and 2 weekend days) with at least 10 waking hours will be required for data analysis [36]. Additionally, the Fitbit can upload real-time step data wirelessly to a web-based database for longitudinal monitoring and data storage (Fitabase) [38]. These data together with the Godin-Shephard Leisure-Time Physical Activity Questionnaire (GSLT-PAQ; described below) will provide a more holistic assessment of PA, as the GSLT-PAQ offers a more qualitative examination, requiring an awareness and perception of one’s PA level.

### Phase 2: Self-Report Survey Assessments

Identification and examination of demographics, perceived physical function, fall risk, health-related QoL, and PA will be conducted in Phase 2 of this study. A summary of the health outcome measures and related ICF domains is presented in Table 1.

### Self-Report Surveys

#### Demographic Characteristics

Demographic variables, including race and ethnicity, state, ZIP code, and sex, will be collected via surveys to support stratified and moderation analyses.

#### SRS-Autism Severity

Autism severity will be assessed using the SRS data available from participants’ enrollment in the SPARK cohort. The SRS is a widely used and validated screening measure of autism-related social impairment [48]. Although prior work suggests some temporal variability in SRS scores [50], with adolescent and adult SRS scores demonstrating moderate-to-good temporal reliability [51], the original date of SRS administration was not available in the SPARK data accessible to this study and will be treated as a limitation.

#### PROMIS-PF Short Form

The 8-item PROMIS-PF short form assesses participants’ self-reported ability to perform physical activities. Developed through rigorous psychometric methods and supported by the NIH, PROMIS measures are validated across diverse populations and health conditions, including cognitive impairment and depression [42,43]. PROMIS-PF provides a standardized, patient-centered measure of functional mobility and is available in multiple languages to accommodate participant preferences. PROMIS will provide a unique added value by providing a measure of patients’ perception of their illness and is useful to clinicians and researchers when attempting to determine factors that may influence health at the level of the individual. PROMIS measures are the result of an initiative supported by the US government through the National Institutes of Health (NIH) to provide psychometrically sound tools for clinical and research purposes with the intent of providing a universal, standardized means of collecting patient-reported information. Furthermore, PROMIS has been demonstrated to be valid and reliable for patients across multiple ethnic and age groups [52] and in a variety of health conditions, including depression [53] and mild cognitive impairment [54]. Incorporating these types of outcome measures into autism research provides innovative means of examining socioenvironmental variables that may influence mobility and how these factors are represented in underserved populations.

#### PROMIS-Global Health

The PROMIS Global Health measure includes 10 items that assess key domains of overall health and well-being [55]. These domains include general health, physical function, pain, fatigue, emotional distress, and social satisfaction. The measure yields 2 summary scores: Global Physical Health (GPH) and Global Mental Health (GMH), both standardized as T-scores based on the US general population. This brief, validated tool is well-suited for remote administration and provides a comprehensive snapshot of participants’ self-reported health status.

#### PROMIS-Instrumental Support

PROMIS-Instrumental Support (PROMIS-IS) will be used to assess perceived social support and interpersonal relationships. The PROMIS measures are scored using T-scores for comparison with the large sample mean corresponding to the development of these measures, with higher scores indicating greater satisfaction or fewer limitations [45].

#### Lower Extremity Functional Scale

The Lower Extremity Functional Scale (LEFS) is a 20-item self-report questionnaire designed to evaluate the functional status of individuals with musculoskeletal conditions affecting the lower limbs [40]. Each item assesses the perceived difficulty in performing common physical activities such as walking, climbing stairs, and engaging in recreational tasks. Responses are scored on a 5-point Likert scale ranging from 0 (extreme difficulty or unable to perform activity) to 4 (no difficulty), with total scores ranging from 0 to 80. Higher scores indicate better lower-extremity function. The LEFS has demonstrated strong psychometric properties, including high reliability, validity, and responsiveness, in both clinical and research settings [40]. However, more recent research has raised concerns about the scale’s content validity, particularly its ability to comprehensively capture all relevant aspects of mobility and function across diverse populations [41]. Considering these limitations, an additional functional survey was incorporated into the protocol to further assess the appropriateness and validity of the LEFS for use in adults with ASD, a population with unique motor and sensory profiles that may not be fully represented by traditional musculoskeletal outcome measures.

#### Fall Risk Scale Assessment Scale

Fall risk was assessed using the US Centers for Disease Control and Prevention (CDC) Stopping Elderly Accidents, Deaths, and Injuries (STEADI) initiative screening questionnaire, a validated clinical tool designed to identify individuals at risk for falls [39,56,57]. The STEADI screener considers multiple contributing factors, including mobility and physical function (eg, balance, gait, strength), medical history (eg, chronic conditions, sensory impairments, and medication use), environmental risks (eg, home safety and assistive device use), and cognitive and mental health status (eg, confusion, depression, and anxiety). Consistent with CDC guidance, total scores were used to stratify fall risk. In this study, a cutoff score of ≥4 was applied to classify participants as having a high fall risk. This threshold has been associated with an increased likelihood of future falls and is commonly used to guide clinical decision-making and fall prevention strategies. The STEADI screening approach is widely implemented in both clinical and community settings and supports the early identification of at-risk individuals, enabling targeted interventions to reduce fall-related morbidity [57,58]. Although not specifically validated in adults with ASD, the screener targets core domains (eg, balance, mobility, fall history, and cognitive factors) that are recognized contributors to fall risk across diverse populations, including individuals with neurodevelopmental and cognitive conditions.

#### Comorbidity Index

The comorbidity burden will be assessed using the weighted Functional Comorbidity Index (w-FCI), a validated tool designed to evaluate the impact of chronic health conditions on functional outcomes in older adults [46]. The w-FCI is an enhancement of the original FCI, which includes 18 conditions scored dichotomously (present/absent). To improve sensitivity to functional impairment, the w-FCI incorporates severity weighting for each condition and includes dementia, a key contributor to functional decline that was omitted in the original index. Each condition will be rated based on its current impact on the participants’ functional status, allowing for a more nuanced assessment of comorbidity. The total score will reflect both the number and severity of conditions, providing a more accurate predictor of rehabilitation outcomes, such as mobility and independence in activities of daily living. The index was selected for its demonstrated predictive validity in geriatric populations and its relevance to functional recovery trajectories.

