### Objectives

This paper presents the protocol for a pilot study designed to evaluate the feasibility, construct validity, and rating reliability of remotely administered physical function assessments in adults with ASD, with attention to racial and ethnic equity in participation and outcomes.

This study has three primary aims:

To evaluate the feasibility, construct validity, and rating reliability of remote physical function assessment in adults with ASD.
Construct validity will be examined primarily through hypothesis testing of the Patient-Reported Outcomes Measurement Information System–Physical Function (PROMIS-PF) measure against related indicators of health and functioning, including habitual PA, lower-extremity functional outcome surveys, fall risk screening surveys, and comorbidity burden. Remote performance-based measures will also be examined as exploratory complementary indicators of physical function. Interrater and intrarater reliability of remote performance scoring will be evaluated using video-recorded assessment sessions scored by multiple raters.To examine racial and ethnic disparities in physical function, PA, fall risk, and QoL among adults with ASD.
This objective is intended to generate preliminary evidence regarding differences in health and functioning across racial and ethnic groups within a telehealth-based study sample.To examine associations among physical function, PA, personal and environmental factors, and QoL, and to evaluate whether these relationships vary by race and ethnicity.
This objective will assess whether physical function and PA are associated with QoL and whether race/ethnicity moderates these relationships.

This protocol is intended to provide foundational evidence for more accessible, equitable, and scalable approaches to physical function assessment in adults with ASD. If the planned hypotheses are supported, the findings may inform future larger-scale studies and telehealth-based rehabilitation strategies aimed at improving physical function, PA, and QoL in this population.

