#### Aim 1: Construct Validity and Reliability of PROMIS-PF

Construct validity of the PROMIS-PF will be examined using a hypothesis-testing framework with related indicators of health and physical functioning consistent with COSMIN (Consensus-Based Standards for the Selection of Health Measurement Instrument) recommendations [59,60]. Predefined hypotheses were specified regarding both the expected direction and magnitude of associations. PROMIS-PF scores (higher scores indicate better perceived physical function) are expected to demonstrate:

Moderate-to-strong positive correlations with other self-reported measures of physical function (eg, LEFS and PROMIS Global Health; r≈0.50-0.70)Moderate positive correlations with habitual PA (steps/day; r≈0.30-0.50)Small-to-moderate negative correlations with comorbidity burden and fall risk indicators (r≈−0.20 to −0.50), where higher scores reflect poorer status.

Associations will be examined using Pearson correlation coefficients when parametric assumptions are met and Spearman rank correlations when assumptions are violated. Correlation coefficients will be reported with 95% CIs, and the interpretation will emphasize agreement with a priori hypotheses [60]. Correlations between PROMIS-PF and other self-report instruments (eg, LEFS and PROMIS Global Health) will be interpreted with caution, as these comparisons are subject to shared method variance, which may inflate associations due to common response tendencies rather than true construct overlap. Accordingly, these analyses will be considered supportive but weaker evidence of convergent validity.

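### The w-FCI total contains a self-rating of functional impact, so its predicted correlation with PROMIS-PF is weakened and ambiguous, though not void, as evidence that comorbidity itself relates to PROMIS-PF

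*Protocol article*

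**What the plan says.** The Objectives section lists the indicators against which PROMIS-PF is to be tested, "including habitual PA, lower-extremity functional outcome surveys, fall risk screening surveys, and comorbidity burden". The Aim 1 analysis section places comorbidity in its own hypothesis together with fall risk, apart from the other self-reports of function: "Small-to-moderate negative correlations with comorbidity burden and fall risk indicators (r≈−0.20 to −0.50), where higher scores reflect poorer status".

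The Comorbidity Index section describes how the score is built. The starting point is a plain list: "The w-FCI is an enhancement of the original FCI, which includes 18 conditions scored dichotomously (present/absent"). The version used here changes that: "To improve sensitivity to functional impairment, the w-FCI incorporates severity weighting for each condition". The rating rule is: "Each condition will be rated based on its current impact on the participants’ functional status, allowing for a more nuanced assessment of comorbidity". On the sum it says: "The total score will reflect both the number and severity of conditions".

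The PROMIS-PF Short Form section describes the measure under test: "The 8-item PROMIS-PF short form assesses participants’ self-reported ability to perform physical activities". Table 1 lists the comorbidity index and the fall-risk screener among the self-report surveys. The fall-risk section adds: "The STEADI screener considers multiple contributing factors, including mobility and physical function (eg, balance, gait, strength").

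Aim 1 does carry a caution about correlations with other self-report instruments, giving LEFS and PROMIS Global Health as examples. Its stated reason is shared method variance from common response tendencies, and it treats such results as supportive but weaker evidence. The article states no analysis using an unweighted condition count.

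**The concern.** The comorbidity hypothesis is useful because comorbidity should be a different construct from self-reported function. A correlation in the expected range would then show that PROMIS-PF behaves as it should towards disease burden. The w-FCI blurs that separation. A participant who sees their function as poor may give higher impact ratings to the same list of conditions. The weighted total then rises as PROMIS-PF falls, even if having those conditions is unrelated to function.

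The full-sample correlations are the primary construct validity analyses. Those with LEFS and PROMIS Global Health are already downgraded, and the performance tests are exploratory at n=25. That leaves steps per day and the comorbidity and fall-risk group. If that group also carries functional content, steps per day is the only full-sample comparator without a self-reported functional component.

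There is a second, conditional consequence. Table 1 classes the index as a personal factor, and Aim 3 allows personal factors into the QoL regression beside PROMIS-PF. If the w-FCI is entered, it may absorb part of the PROMIS-PF coefficient.

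**Working it through.** **The plan's own figure.** Fisher z, power = Φ(atanh(r)·√(n−3) − 1.96), with n = 155 and √152 = 12.33:

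- r = 0.25: 0.2554 × 12.33 − 1.96 = 1.19, power 0.88.
- r = 0.30: 0.3095 × 12.33 − 1.96 = 1.86, power 0.97.

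The statement that N=155 is adequate for r of 0.25 to 0.30 is reproduced, and this point does not affect it. Two related values help in reading the result. The smallest correlation significant at two-sided 0.05 is tanh(1.96/12.33) = 0.158. At the weak end of the hypothesis, |r| = 0.20, power is 0.705 and the 95% CI is about 0.04 to 0.35 in absolute value.

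**How large the built-in part could be.** The article gives no w-FCI distribution, so every input below except the number of conditions is an assumption.

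- K = 19 conditions (the original 18 plus dementia).
- Each condition is present with probability p, independently of PROMIS-PF. The true correlation of PROMIS-PF with the count is therefore zero.
- Each present condition has a three-level rating w, cut at ±0.43 from a latent impact that correlates −ρ with standardised PROMIS-PF.

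With T the weighted total and m the mean rating given PROMIS-PF:

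- c = Cov(PF, w) = −ρ × 2φ(0.43) = −ρ × 2 × 0.3637 = −0.7274ρ
- Cov(PF, T) = K·p·c
- Var(T) = K(p·E[w²] − p²·E[m²]) + K²p²·Var(m), with Var(m) ≈ c²

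Worked case, p = 0.15 and ρ = 0.3: c = −0.2182, Kp = 2.85, Cov = −0.622.

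- Ratings 0–2: E[w²] = 5/3 and E[m²] ≈ 1.048. Var(T) ≈ 19 × (0.2500 − 0.0236) + 8.1225 × 0.0476 = 4.69. r = −0.622/2.166 = **−0.29**.
- Ratings 1–3: E[w²] = 14/3 and E[m²] ≈ 4.048. Var(T) ≈ 19 × (0.7000 − 0.0911) + 0.387 = 11.96. r = −0.622/3.458 = **−0.18**.

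Simulation with 400,000 draws gave −0.286 and −0.178. Other settings:

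| p | ρ | ratings 0–2 | ratings 1–3 |
|---|---|---|---|
| 0.08 | 0.2 | −0.14 | −0.09 |
| 0.08 | 0.3 | −0.21 | −0.13 |
| 0.08 | 0.5 | −0.34 | −0.21 |
| 0.15 | 0.2 | −0.20 | −0.12 |
| 0.15 | 0.3 | −0.29 | −0.18 |
| 0.15 | 0.5 | −0.45 | −0.29 |
| 0.25 | 0.2 | −0.26 | −0.16 |
| 0.25 | 0.3 | −0.37 | −0.24 |
| 0.25 | 0.5 | −0.56 | −0.38 |

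A weaker link gives little. Take a Poisson number of conditions with mean 2, ratings 1–3 and ρ = 0.1. Then Cov = 2 × (−0.0727) = −0.145, Var = 2 × 14/3 + 4 × 0.0053 = 9.35, and r = −0.145/3.058 = −0.05. A much stronger link (ρ = 0.7) gives −0.29 to −0.69 over the same prevalences and scales. At ρ = 0 the built-in part is zero.

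The rating step alone can therefore place the result inside the predicted band, but it need not.

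**A limit on the remedy.** If the form recorded only an impact rating, and zero can mean present without impact, a count of non-zero ratings still carries some functional content. In the worked case, Cov = 2.85 × (−0.3 × 0.3637) = −0.311, Var ≈ 19 × (0.0999 − 0.0103) + 8.1225 × 0.0119 = 1.80, and r = −0.311/1.342 = −0.23, against −0.29 for the weighted total. A count from a separate presence item would give zero here.

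**The case against.** The strongest reply has four parts.

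First, convergent hypotheses expect related constructs to overlap. The total also depends on how many conditions there are, and the rating is made condition by condition, not on the PROMIS-PF activities. This stands. A reader might infer that the correlation is guaranteed and so cannot count as evidence of validity. The documents do not support that, because impact is only part of the score and its share is unknown.

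Second, the Aim 1 caution gives its instruments only as examples, and Table 1 places the w-FCI among the self-report surveys, so the caution may already apply. This stands in part. The w-FCI is not named, and the caution concerns response style. Functional content written into the score is a different matter and would remain even with unbiased answers.

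Third, the illustration is artificial. It lets impact ratings follow PROMIS-PF while the number of conditions does not, and if the ratings are accurate, the conditions really do limit function. This also stands. The calculation shows what is possible, not what is likely.

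Fourth, the consequence is bounded. Comorbidity shares one of three full-sample hypothesis groups, steps per day is unaffected, and the study calls itself hypothesis-generating. The covariates named for Aims 2 and 3 are sex and autism severity, so the Aim 3 effect arises only if the w-FCI is entered as a personal factor. All of this limits the weight of the point without removing it.

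A reader might also conclude that the w-FCI should be dropped as the comparator, or STEADI split by item. Neither follows. The w-FCI is the prespecified index and is described as validated, and the article gives STEADI's domains but not its items.

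**Conclusion.** The point holds in a limited form. A w-FCI correlation between −0.20 and −0.50 is weakened and ambiguous evidence that comorbidity itself relates to PROMIS-PF. It is not void. That the score contains a functional rating rests on the protocol's own description and needs no assumption.

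The size of the built-in part cannot be determined from the documents. Under the assumed inputs it runs from about −0.05 to −0.56 for latent correlations of 0.1 to 0.5, so from trivial to beyond the strong end of the band. For STEADI the overlap is partial, since physical function is one of several domains described. The effect on Aim 3 is conditional on the w-FCI entering the model. No sample-size or power statement changes.

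**What to change.** 1. In Aim 1, report the correlation of PROMIS-PF with the unweighted number of conditions present beside the w-FCI correlation, each with its 95% CI. Call the comorbidity hypothesis clearly supported only if the count also correlates in the predicted direction. Near zero, the CI at N=155 is about ±0.16 (1.96/√152), so read the interval as well as the sign.
2. State how presence is taken from the form. Use a recorded presence item if there is one. Otherwise count non-zero ratings and say that this removes only part of the functional content.
3. Extend the Aim 1 caution to name the w-FCI, and STEADI in part, for overlap of functional content as well as response style.
4. If comorbidity enters the Aim 3 model with PROMIS-PF, add a sensitivity model using the count.

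The cost is a few lines of analysis text and one or two extra estimates, with data collection already complete. It depends on presence being recoverable from the form, which the article implies but does not show. The downside is that the count ignores severity and will probably give a smaller correlation.
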